# Effect of Liuzijue on pulmonary rehabilitation in patients with chronic obstructive pulmonary disease: study protocol for a multicenter, non-randomized, prospective study

**DOI:** 10.1186/s12906-022-03789-6

**Published:** 2022-11-17

**Keywords:** Chronic obstructive pulmonary disease, Liuzijue, Pulmonary rehabilitation

## Abstract

**Background:**

Traditional Chinese exercise as a new pulmonary rehabilitation technique has been increasingly used and achieved good results in pulmonary rehabilitation of chronic obstructive pulmonary disease (COPD). The aim of this study is to investigate the protective effects of Liuzijue on exercise tolerance, lung function, and quality of life in patients with COPD.

**Methods:**

This study is a multicenter, non-randomized, prospective study. Patients will be divided into a control group (CG) and a Liuzijue group (LG) based on their willingness to learn Liuzijue. None of the outcome assessors will know the grouping of patients. Participants in this study will be collected from stable COPD patients who are outpatients or inpatients in 3 centers in China since September 2021. Patients will meet the diagnostic criteria for GOLD stage I-II COPD (FEV_1_% ≥ 0.5 and FEV_1_/FVC < 0.7) and be aged 40 years or older. Patients voluntarily will take part in the clinical study and sign an informed consent form. All participants will follow their existing medication. For LG patients, Liuzijue training has been added. Patients will practice Liuzijue for more than 30 minutes a day, more than 5 days a week, and adhere to the training for 3 months. Outcome indicators are 6-minute walk test (6MWT), lung function (FEV_1_%, FEV_1_/FVC, MMEF, PEF), modified British Medical Research Council (mMRC) score, COPD assessment test score (CAT), acute exacerbations and changes in drug treatment.

**Discussion:**

This study quantified the effect of Liuzijue on the pulmonary rehabilitation of COPD patients in the stable phase of the disease, and provided a basis for the use of Liuzijue in COPD patients.

**Trial registration:**

Chinese clinical trial registry, ChiCTR2100048945. Date: 2021-07-19. http://www.chictr.org.cn/showproj.aspx?proj=129094

**Supplementary Information:**

The online version contains supplementary material available at 10.1186/s12906-022-03789-6.

## Background

Chronic obstructive pulmonary disease (COPD) is a group of respiratory diseases characterized by airflow limitation. It has a progressive course with high morbidity and mortality. However, outcomes of drug treatment remain limited. It therefore causes a huge family and social burden and is an important public health problem [1]. An epidemiological survey of COPD in China published in The Lancet in 2018 found that the prevalence of COPD in people aged 40 years or older was 13.7% [2]. WHO predicts that by 2030, 4.5 million people will die from COPD each year, making it a major global public health problem [3, 4]. The focus of COPD treatment has gradually shifted from the acute exacerbation phase to the stabilization phase. How to further prevent and treat COPD so as to improve the quality of life of patients has been widely concerned by society and the medical community.

The American Thoracic Society (AST) and the European Respiratory Society (ERS) have recommended early pulmonary rehabilitation using exercise training for COPD patients [5]. Pulmonary rehabilitation has many advantages, such as improving life quality and exercise capacity, improving psychological conditions and reducing mortality [6]. However, less than 10% of COPD patients have access to pulmonary rehabilitation services [7, 8]. There are many reasons for this phenomenon, such as shortage of healthcare professionals, single exercise modality, the need for special equipment and fixed places, and the cost of equipment maintenance. All these problems have led to low patient compliance with exercise training, reducing the accessibility and feasibility of pulmonary rehabilitation [9–13]. Therefore, a convenient and effective rehabilitation technique is needed to meet the rehabilitation demand of COPD patients.

Liuzijue originated from Taoism in China. The earliest treatise on the Liuzijue was first published in Tao Hongjing’s “The Yang Xing Yan Ming Lu” during the Northern and Southern Dynasties, about 1500 years ago. In 2007, Liuzijue was reorganized by the General Administration of Sport of China and formed a complete set of standard qigong training methods. This method covers aspects of modern pulmonary rehabilitation, such as exercise training, respiratory muscle training and psychological rehabilitation, and meets the basic requirements of pulmonary rehabilitation. The characteristics of the Liuzijue are: (1) Liuzijue is to exhale through reading the specific 6-word of “xu”, “he”, “hu”, “si”, “chui”, and “xi”. (2) The Liuzijue uses deep and slow breathing and reverse abdominal breathing to exercise the function of the respiratory muscles. (3) The physical movements in Liuzijue exercise the muscles of the whole body, especially the skeletal muscles of the upper and lower limbs. (4) Liuzijue enhances the patient’s mental conditioning during the training process.

Safety, efficiency, and economy are the strengths of Liuzijue. In terms of safety, the movements of Liuzijue are simple and easy to perform, the exercise load is not too heavy and the amount and duration of exercise is easy to control. In terms of effectiveness, the rehabilitation effects of Liuzijue have been confirmed by several studies. Meta-analyses have shown that Liuzijue improves the St. George’s respiratory questionnaire score (SGRQ), COPD assessment test score (CAT), modified British Medical Research Council (mMRC) score, 6-minute walking test (6MWT), percentage of forced expiratory volume in 1 second to predicted value (FEV_1_%), and ratio of forced expiratory volume in 1 second to forced vital capacity (FEV_1_/FVC) in COPD patients [14–16]. The results show that Liuzijue could improve the quality of life, exercise tolerance and lung function in COPD patients. In terms of economy, learning Liuzijue is inexpensive, with a few movements and easy to master. There is no requirement for venue and facilities for Liuzijue, which is easy to implement and low-cost.

Therefore, in this study, Liuzijue is used for pulmonary rehabilitation exercises in stable COPD patients. This study investigates the effects of Liuzijue on exercise endurance, lung function, quality of life in COPD patients. This will lead to the search for a more effective, inexpensive and easy method of respiratory rehabilitation training to be applied to patients in the community and at home.

## Methods/design

### Study design

This study is a multicenter, non-randomized, prospective study. There are 3 centers in this study, including the First Affiliated Hospital of Zhejiang Chinese Medicine University, the Affiliated Hospital of Jiangxi University of Traditional Chinese Medicine and the Affiliated Hospital of Chengdu University of Traditional Chinese Medicine. Patients will be divided into a control group (CG) and a Liuzijue group (LG) based on their willingness to learn Liuzijue. None of the outcome assessors will know the grouping of the patients. Participants in this study will be collected from stable COPD patients who are outpatients or inpatients since September 2021. The protocol has been registered in the China Clinical Trial Registry (registration number: ChiCTR2100048945) and approved by the Ethics Committee of Zhejiang Provincial Hospital of Chinese Medicine (Ethics number: 2019-KL-095-06). Informed consent will be obtained from all participants before they participate in the study. The research process is shown in Fig. 1, and the time point of the research is shown in Fig. 2. The protocol follows the SPIRIT 2013 checklist, provided in Additional file 1: SPIRIT 2013 checklist.

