### Sample size

The sample size is calculated based on the primary outcome (6MWT) using PASS15.0 software. According to the previous literature [17], the mean for the control group is estimated to be 418.71 with a standard deviation of 66.19. After Liuzijue exercising, the mean for the experimental group is 483.62 with a standard error of 67.30. With a power of 80% and an alpha of 5% (two-sided), the minimum sample size per group is 23. Given a drop-out rate of 20%, the minimum sample size in total is 46.

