### Outcome measurement

The primary outcomes is 6-minute walking test (6MWT). Secondary outcomes include pulmonary function tests (FEV1%, FEV1/FVC, MMEF, PEF), CAT score and mMRC score. Pulmonary function tests are performed by specialists. 6MWT is performed by trained research team members. Symptoms of breathlessness will be assessed using the mMRC and the CAT questionnaire will be used to assess quality of life. If the patient has an acute exacerbation, it will be recorded. Any changes in drug treatment of the patients will also be recorded. None of the outcome assessors will be aware of the patients’ grouping.

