### Statistical analysis

Statistical analysis of the data will be performed using SPSS Statistics 26.0. Continuous variables with normal distribution will be described by mean and standard deviation. Continuous variables with non-normal distribution or ordinal variables will be described by median and interquartile range. Categorized variables will be summarized as counts and proportions. Continuous variables will be compared using Student’s t-test (normal distribution) or the Mann-Whitney U test / Wilcoxon rank test (abnormal distribution). Ordinal variables will be compared using Mann-Whitney U test/ Wilcoxon rank test. The categorical variables will be compared using Fisher’s exact test or the chi-squared test. Training-related effects will be assessed using a repeated ANOVA. All reported *P* values are two-sided, and *P* values < 0.05 is considered statistically significant.

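### Patients at three centres choose their own group and the named between-group tests cannot include centre, so any centre difference in both uptake and outcome would confound the 6MWT comparison

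*Protocol article*

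**What the plan says.** Under Study design the article states "There are 3 centers in this study" and "Patients will be divided into a control group (CG) and a Liuzijue group (LG) based on their willingness to learn Liuzijue". It describes no allocation ratio, quota, matching or stratification by centre.

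Under Outcome measurement, 6MWT is the single primary outcome, and "6MWT is performed by trained research team members". Assessors are to be unaware of group.

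Under Statistical analysis the tests are given by type of variable: "Continuous variables will be compared using Student’s t-test (normal distribution) or the Mann-Whitney U test / Wilcoxon rank test (abnormal distribution"; "The categorical variables will be compared using Fisher’s exact test or the chi-squared test"; and "Training-related effects will be assessed using a repeated ANOVA". The section does not say whether the two-sample tests apply to follow-up values or to changes. It lists no factors for the ANOVA.

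The Sample size section is a plain two-group calculation for 6MWT. The limitations listed in the discussion cover blinding of participants, compliance at home and uptake in other countries. They mention neither self-selection nor centre.

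**The concern.** In a trial randomised within centre, leaving centre out mainly costs precision, because the design keeps the groups similar across centres. Here patients choose, so the Liuzijue-to-control ratio in each centre is whatever local preference makes it.

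Centres may also differ in walking distance at follow-up, or in how patients change over the study. If both differ, centre is a confounder. A centre with longer walks and more willing patients would produce a group difference with no training effect; the reverse pattern would hide a real one. Blinded assessors do not protect against this.

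The two-sample and chi-squared tests as named cannot separate the two sources. At stake is whether the main 6MWT estimate can be read as an effect of Liuzijue.

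**Working it through.** **Inputs from the article (Sample size).** Control mean 418.71, SD 66.19; Liuzijue mean 483.62, spread 67.30 (called a standard error there, but the stated size reproduces only if it is read as an SD); two-sided 5%; power 80%; 23 per group; 20% drop-out; 46 in total.

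**Step 1: reproduce the plan's figure.**
- Difference = 483.62 − 418.71 = 64.91 m.
- SD = √((66.19² + 67.30²)/2) = 66.75 m; standardised difference 64.91/66.75 = 0.97.
- Noncentral t: 18 per group gives power 0.809 (17 gives 0.785).
- 18/0.8 = 22.5, rounded up to 23; 2 × 23 = 46.

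The stated size reproduces, includes drop-out, and contains no centre term.

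**Step 2: bias without a centre term.** The article gives no centre means and no uptake by centre, so these are assumptions: three equal centres; offsets +g/2, 0, −g/2, where g is the spread between the highest and lowest centre; Liuzijue shares 0.5+a, 0.5, 0.5−a.

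Bias = Σp·o/Σp − Σ(1−p)·o/Σ(1−p) = 4ag/3.

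Example, a = 0.3 and g = 60: Liuzijue mean offset (0.8×30 − 0.2×30)/1.5 = +12; control (0.2×30 − 0.8×30)/1.5 = −12; bias 24 m, and 24/64.91 = 37%.

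The false-positive rate comes from the noncentral t with 18 per group and SD 66.75. Each cell shows bias and rate:

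| Liuzijue shares | spread 20 m | spread 40 m | spread 60 m |
|---|---|---|---|
| 50/50/50% | 0 m; 5.0% | 0 m; 5.0% | 0 m; 5.0% |
| 60/50/40% | 2.7 m; 5.2% | 5.3 m; 5.6% | 8.0 m; 6.4% |
| 70/50/30% | 5.3 m; 5.6% | 10.7 m; 7.5% | 16.0 m; 10.8% |
| 80/50/20% | 8.0 m; 6.4% | 16.0 m; 10.8% | 24.0 m; 18.2% |

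The sign depends on which centre has the higher uptake.

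**Step 3: which analysis is exposed.** A t-test on follow-up 6MWT carries the whole bias. A group-by-time contrast in a repeated ANOVA, or a test of change, removes centre differences that stay constant over time. Only differences between centres in change remain. The article gives no SD of change, so the error rates above do not carry over to that case.

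**Step 4: cost of adjusting.** With centre as a fixed factor, 2 degrees of freedom are lost and the variance of the effect is multiplied by 1/(1−R²), where R² = mean((p−0.5)²)/0.25 is the share of group membership explained by centre. At 70/50/30%: R² = ((0.04 + 0 + 0.04)/3)/0.25 = 0.107, and 1/0.893 = 1.12.

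| Liuzijue shares | variance factor | power with 18 per group | completers per group for 80% | enrolled in total |
|---|---|---|---|---|
| 50/50/50% | 1.00 | 0.808 | 18 | 46 |
| 60/50/40% | 1.03 | 0.797 | 19 | 48 |
| 70/50/30% | 1.12 | 0.762 | 20 | 50 |
| 80/50/20% | 1.32 | 0.694 | 23 | 58 |

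The residual SD is held at 66.75. Adjusting for baseline 6MWT would be expected to lower it, but the article gives no figure for how much.

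**The case against.** The strongest objection is that this rests partly on silence. The article does not say that centre will be ignored. It lists no factors for the ANOVA, and a full protocol or analysis plan, not shown here, could add centre. That stands for the ANOVA. It does not dispose of the point, because the t, rank, Fisher and chi-squared tests are named for each type of variable and cannot hold a centre term as written.

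A reader might infer that the group mix will differ by hospital, or that each hospital has its own walking course and spirometer. The documents support neither. They say only who performs the tests, and they describe a taught course with video and a common applet. With equal uptake the bias is zero whatever the centres' levels. Differences in how the course is taught would reach only Liuzijue patients; they would alter the effect between centres and are not a spurious group difference.

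The ANOVA is the analysis assigned to training effects. If it is read as a group-by-time contrast, stable centre differences cancel. That also stands and narrows the exposure.

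Finally, the large figures need large inputs. A 60 m spread is close to the whole planned effect, and as a difference in change it would be extreme. At the low end, a few metres and a rate just above 5%, the problem is small.

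**Conclusion.** The point holds as a conditional weakness. Self-selected groups at three centres are to be compared with tests that cannot include centre, and nothing stated would remove a centre imbalance if one arose. Confounding needs centre differences in both uptake and outcome, and the documents inform neither.

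Over the assumed ranges the bias in an unadjusted follow-up comparison runs from nil to about a third of the planned difference. The error rates rest on equal centre sizes, an SD of 66.75 m and 18 completers per group. They are illustrations and not a forecast for this trial. The documents do not support the stronger claim that the planned analysis has a known inflated error rate.

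The correction is worth making because centre is known for every patient.

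**What to change.** In Statistical analysis, name the model for the primary 6MWT comparison and include centre (3 levels) as a fixed factor alongside baseline 6MWT. Do the same for the other continuous outcomes, each with its own baseline. Report Liuzijue and control numbers and mean 6MWT by centre, so that readers can see whether uptake or walking distance differed.

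I would not extend this to centre-stratified rank and categorical tests: 46 patients over three centres is about 15 per centre, and the gain from such sparse strata is debatable.

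The cost is a change of wording, 2 degrees of freedom and, if uptake is unequal, some precision: the variance of the effect is about 12% higher at 70/50/30%, which raises the need from 18 to 20 completers per group. That loss is largest when uptake is most unequal, which is also when an unadjusted comparison is most open to centre bias. A centre term does not deal with differences between willing and unwilling patients within a centre; that part of the self-selection problem remains.

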**Fig. 1 Fig1:**
[figure not shown]
Study flow chart

**Fig. 2 Fig2:**
[figure not shown]
Illustration of the design

### Sample size

The sample size is calculated based on the primary outcome (6MWT) using PASS15.0 software. According to the previous literature [17], the mean for the control group is estimated to be 418.71 with a standard deviation of 66.19. After Liuzijue exercising, the mean for the experimental group is 483.62 with a standard error of 67.30. With a power of 80% and an alpha of 5% (two-sided), the minimum sample size per group is 23. Given a drop-out rate of 20%, the minimum sample size in total is 46.

### Participants

Patients diagnosed with stable COPD in the outpatient or inpatient department of 3 centers from September 2021 are enrolled in this study. Individuals interested in the study participate with the study.

Inclusion criteria: (1) Meet COPD diagnostic criteria. (2) FEV1% ≥ 0.5, and FEV1/FVC < 0.7 (3) Age above 40 years. (4) Patients voluntarily participated and signed an informed consent form. Exclusion criteria: (1) Patients with serious primary diseases such as cardiac, hepatic, renal, cerebral and hematopoietic system. (2) Patients with localized giant bullae of lung, pneumothorax and extreme physical weakness or disability. (3) Pregnant or lactating women. (4) Psychiatric patients. (5) Unwilling to accept study measures or otherwise unable to cooperate. (6) Patients who are currently participating in other drug-related clinical trials or intervention studies.

### Intervention

All patients continue to take their current medication and receive health education on the self-management of COPD. Patients are advised to quit smoking and get vaccinated against pneumonia and flu. LG group receive 60 minutes of Liuzijue course, where patients learn Liuzijue through video and face-to-face instruction. Patients then exercise Liuzijue at home for 30 minutes or more a day, more than 5 days a week for 3 months.

### Follow-up

General information and observations will be collected from patients at the time they join the study. For the LG group, follow-up visits will be made once a week (telephone or WeChat) for the first 1 month and once every 2 weeks (telephone or WeChat) for the next 2 months after enrolment. By means of follow-up visit, patients will be reminded to exercise Liuzijue, and researchers can get to know the changes in their health condition and promptly help them to overcome the difficulties encountered in the process of exercising. Field follow-up visits is conducted 3 months and 6 months after admission to record changes in the patient’s outcome indicators for both CG and LG.

Patients will be followed up using a WeChat applet. The applet will help patients to clock in for training, do self-test health scales, upload and view test reports, initiate consultations with doctors, view health information and record acute exacerbations. Through the platform, doctors can view patients’ records such as punch cards, scale assessments and test reports, and contact patients for follow-up visits. At the end of each training session, patients will be asked to make a record on the applet. Furthermore, the number of follow-up visits is flexibly adjusted according to the patient’s punch card records.

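### Only the Liuzijue group has scheduled calls, so its exacerbations and drug changes have more chances to be recorded, and the contrast is Liuzijue plus support against usual care

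*Protocol article*

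**What the plan says.** All references are to the protocol article.

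- **Follow-up, remote contacts.** The schedule is assigned to the Liuzijue group (LG): "For the LG group, follow-up visits will be made once a week (telephone or WeChat) for the first 1 month", and then "once every 2 weeks (telephone or WeChat) for the next 2 months after enrolment". Through these contacts patients are reminded to exercise, "researchers can get to know the changes in their health condition", and staff can "promptly help them to overcome the difficulties encountered in the process of exercising". The number of contacts may be adjusted according to training records.
- **Follow-up, field visits.** Outcome indicators are recorded in both LG and the control group (CG) at 3 and 6 months.
- **Follow-up, applet.** It is described for patients in general and includes self-recording of exacerbations and consultations with doctors. Recording drug changes is not among its listed functions. One prompt to use it is tied to training: "At the end of each training session, patients will be asked to make a record on the applet".
- **Abstract, Methods.** The outcome indicators include "acute exacerbations and changes in drug treatment".
- **Outcome measurement.** On exacerbations: "If the patient has an acute exacerbation, it will be recorded". Drug changes are treated in the same way. Neither has a stated source, interval or method. The primary outcome is the 6-minute walk test (6MWT), and assessors are unaware of grouping.
- **Discuss, limitations.** Unblinded participants and lower compliance at home are named, with timely follow-up and encouragement for low compliers. Unequal contact is not mentioned.

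**The concern.** The LG-only contacts do two things at once.

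First, they are surveillance. A researcher who speaks to a patient every week or two will hear of exacerbations and prescription changes that a control patient must remember, or enter unprompted, before a visit at 3 months. Exacerbations and drug changes are outcome indicators, and nothing confines their recording to the occasions that both groups share. A count that mixes sources would then compare well-observed LG patients with less-observed CG patients.

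Second, they are support. Reminders, problem-solving and regular professional attention can influence how far a patient walks and how an unblinded patient answers CAT and mMRC. The stated aim is the effect of Liuzijue, but the groups differ in both the exercise and the support.

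At stake are the fairness of the two event comparisons and the wording of any conclusion about 6MWT, CAT and mMRC.

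**Working it through.** **Design figure in the plan.** The only one is the 6MWT sample size, which this point does not affect. It reproduces: difference 483.62 − 418.71 = 64.91; pooled SD √[(66.19² + 67.30²)/2] = 66.75, reading the second spread as an SD. A two-sided 5% t-test at 80% power needs 17.6, so 18 per group. 18/0.8 = 22.5, so 23 per group and 46 in total.

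**Scheduled contacts, from the Follow-up section.**

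- Month 1, weekly: 4. Months 2 and 3, every two weeks: 8 weeks / 2 = 4. Remote total: 4 + 4 = 8. With calendar months of 30.4 days it is 30.4/7 + 60.8/14 = 4.34 + 4.34 = 8.7, so about 8 is a fair summary.

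| Scheduled contacts after enrolment | LG | CG |
|---|---|---|
| To month 3 | 8 remote + 1 visit = 9 | 0 remote + 1 visit = 1 |
| To month 6 | 8 remote + 2 visits = 10 | 0 remote + 2 visits = 2 |

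**Channels by which an event can reach the record.**

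| Channel | LG | CG |
|---|---|---|
| Field visits at 3 and 6 months | yes | yes |
| Applet self-record (exacerbations) | yes, with a prompt to open the applet after each session | apparently yes, with no training session to prompt it |
| Scheduled calls or messages | about 8 | none described |

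The gap is likely to be widest for drug changes, which the applet does not list.

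**What unequal capture would do.** Let p be the true risk, the same in both groups, and let c be the proportion of events captured. If every recorded event is real:

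apparent risk ratio = (p × c_LG) / (p × c_CG) = c_LG / c_CG

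The ratio does not depend on p. The documents give no capture rates, so these are assumed, with c_LG = 95% and p = 20% for illustration:

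| c_CG | Recorded risk LG | Recorded risk CG | Apparent ratio |
|---|---|---|---|
| 95% | 19% | 19% | 0.95/0.95 = 1.00 |
| 80% | 19% | 16% | 0.95/0.80 = 1.19 |
| 60% | 19% | 12% | 0.95/0.60 = 1.58 |

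Conversely, a true ratio of 0.80/0.95 = 0.84 in the second row, or 0.60/0.95 = 0.63 in the third, would appear as no difference.

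**Which outcomes are touched.** 6MWT is measured at the common visits by assessors unaware of grouping, so unequal capture does not arise. The support given to LG can still affect 6MWT, and also CAT and mMRC. Detection bias on events would count against LG, while support would probably favour it.

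**The case against.** The best case for the plan starts from its field visits. The Follow-up section says outcome indicators are recorded at 3 and 6 months in both groups, and the Abstract counts exacerbations and drug changes among those indicators. Read together, the recording occasions are the same for LG and CG. The calls are described as reminders, health checks and help, not as data collection. A recall form and a source rule are details that a condensed article may leave to the full protocol. Support is a natural part of a home programme, and a supported programme against usual care is a legitimate pragmatic contrast. Exacerbations and drug changes are also not in the list of secondary outcomes in Outcome measurement.

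Much of this stands, and it rules out several stronger readings that a reader might infer:

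- *Events are captured unequally.* The documents show unequal opportunity. They do not say that call reports enter the outcome record.
- *Controls have no contact for 3 months.* Only scheduled contact is missing from the description. The applet is not restricted to LG and offers self-recording and consultation.
- *The number of LG contacts only goes up.* The Follow-up section says adjusted, without a direction. The limitations paragraph supports more contact for low compliers, but that does not exclude fewer for others.
- *The primary outcome suffers detection bias.* It does not, for the reason given in the working.

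What the objection does not remove is the open source rule. The article states the LG-only schedule, says that health changes are learned through it, lets exacerbations be recorded on the applet, and then says only that events will be recorded. A team following this text could properly enter an event first heard of in a call. Blinded assessors cannot restore a CG event that nobody reported. If support is meant as part of the intervention, the article does not say so.

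**Conclusion.** The point holds as one of unequal opportunity for detection and of an unnamed part of the contrast. The schedule gives LG about 8 remote contacts and CG none described in the first 3 months. For exacerbations and drug changes the resulting bias has unknown size: the ratios of 1.00, 1.19 and 1.58 rest wholly on assumed capture rates, and the first applies if the common channels work equally well in both groups. For 6MWT, CAT and mMRC the design estimates Liuzijue plus supported follow-up against usual care, not Liuzijue alone. The net direction across the two mechanisms is unknown.

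A reader might conclude that equal calls would let the trial attribute a difference to Liuzijue itself. They would not: patients choose their group by whether they want to learn the exercise, which is a separate threat to attribution. Nor can unequal contact be presented as the main obstacle to attribution.

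The point deserves action because the change is cheap and the two event comparisons are otherwise hard to interpret.

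**What to change.** 1. At the existing 3- and 6-month visits, collect exacerbations and drug changes in both groups with one identical structured recall form, supplemented by medical and prescription records.
2. State that the between-group comparison of these events uses that source only. Use events learned from calls or the applet for care and for description.
3. Describe the comparison throughout as Liuzijue plus supported follow-up against usual care, and add unequal contact to the limitations.

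The cost is one form at visits that already take place and a few sentences of text. The downside is small: some events known only from calls or the applet are left out of the comparison.

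Giving CG a matching number of short contacts without training content would narrow the difference in attention. It needs extra resources (about 8 messages per control patient) and is a matter of design preference, so it is an option and not part of the request.
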